## Abstract

**Background:**

Acute exacerbation is a common cause of hospitalization in patients with chronic heart failure, and coronary heart disease is the most common cause. Shenfu injection, a Traditional Chinese Medicine injection, widely used in the adjuvant treatment of patients with acute exacerbation of chronic heart failure, shows some treatment effect in improving the symptoms and the quality of life, but it lacks the rigorous clinical evaluation of research reports. This paper describes the protocol for the clinical assessment of Shenfu injection loading in the treatment of patients with acute exacerbation of chronic heart failure.

**Methods:**

This protocol adopts the design of a prospective, randomized, multicenter, blind imitation, placebo-controlled trial to assess the efficacy and safety of Shenfu injection loading in the treatment of patients with acute exacerbation of chronic heart failure due to coronary heart disease. The research will be carried out in 12 hospitals in China and is expected to enroll 160 inpatients with acute exacerbation of chronic heart failure due to coronary heart disease (*yang* and *qi* deficiency syndrome). On the basis of the conventional therapy of western medicine, patients will be randomized to either the treatment group (100 ml 5% glucose injection + 50 ml Shenfu injection) or the control group (150 ml 5% glucose injection) for 7 ± 1 days and follow-up for 28 ± 3 days. The primary outcomes are New York Heart Association cardiac function classification and Traditional Chinese Medicine syndromes. The secondary outcomes are left ventricular ejection fraction, brain natriuretic peptide level, Lee’s heart failure score, 6-minute walking distance, and the incidence and readmission rate of cardiovascular events (including the emergency rate due to acute exacerbation of chronic heart failure).

**Discussion:**

This trial will assess the effect of loading Shenfu injection in the treatment of patients with acute exacerbation of chronic heart failure caused by coronary heart disease (*yang-qi* deficiency syndrome) on the symptoms and signs of heart failure, exercise tolerance, and other aspects, and observe its influence on the short-term prognosis with follow-up. The results of the study will provide clinical research evidence for application of Shenfu injection in the treatment.

**Trial registration:**

This trial was registered on 26 December 2012 at the Chinese Clinical Trials Register (Identifier: ChiCTR-TRC-12002857).

**Electronic supplementary material:**

The online version of this article (doi:10.1186/s13063-015-0729-7) contains supplementary material, which is available to authorized users.

## Background

Chronic Heart failure (CHF) is a chronic progressive disease, the terminal stage of various cardiovascular diseases and a cardiac dysfunction syndrome. The condition of CHF patients will remain stable after treatment, but will also dramatically worsen under the influence of various factors (such as infection, rapid ventricular rate arrhythmia, and so forth) and appears as acute decompensated CHF (that is, acute exacerbation of CHF (AECHF)) [1].

The first guideline for diagnosis and treatment of acute heart failure (AHF) in China was promulgated in March 2010 [2]. “AHF” referred to sudden onset or acute exacerbation of the original CHF, expanding the scope of AHF, and acute decompensation of CHF was included. *The diagnosis and treatment guideline for heart failure of China in 2014* [3] indicates that AHF is the main cause of hospitalization in patients whose age has exceeded 65 years, most of them with acute exacerbation based on the original CHF.

A study [4] which retrospectively analyzed 10,714 hospitalized cases retrieved from 42 hospitals in China over three different time periods (the 1980s, 1990s, and 2000s) showed that patients hospitalized for CHF accounted for about 16.3 to 17.9% of those with cardiovascular disease. The primary cause of CHF was coronary heart disease (CHD), most of the cardiac function of HF was grade III(42.5 to 43.7%),and the main cause of death in heart failure patients was left heart failure (59%).

The treatment for AECHF, according to the guideline [3], which is the same as the treatment for AHF, includes: general treatment (such as oxygen therapy, controlling the intake and output, and so forth); medical treatment (such as diuretics which can reduce cardiac load and improve symptoms); treatment with drugs or/and non-drug therapy for the main disease and complications depending on patient’s conditions. The symptoms of AECHF can be alleviated over a short period using simple western medicine treatment, shown by improvement in heart function, hemodynamic indices and biological indices. Presently, Traditional Chinese Medicine (TCM) treatment for AECHF is still secondary to western medicine, and TCM injection, such as Shenfu injection (SFI) [5] and Shenmai injection [6] ,are commonly used by TCM syndrome.

A retrospective study [7] showed that the main TCM syndrome of CHF was deficiency of *qi*, with *yang* or/and *yin*. The result of a TCM syndrome survey [8] showed that CHF was divided into two types: *qi-yang* deficiency with blood stasis and/or phlegm retention; and *qi-yin* deficiency with blood stasis and/or phlegm retention. The pattern of syndrome change [9] was *qi* deficiency → *qi* deficiency, *qi-yin* deficiency →*qi-yang* deficiency with blood stasis and/or phlegm retention.

Based on the ancient prescription of Shenfu Decoction, SFI is composed of the extracts of red ginseng and Radix Aconiti Lateralis Preparata using modern technology. The active ingredients include Ginsenoside and Aconitine [10], which have the function of supplementing *qi*, avoiding collapse and reviving *yang*. SFI was an officially approved product in 1987 (approval code: certification number Z20043117; norm: 50 ml per bottle). Many clinical reports indicated that SFI was convenient for emergency use and had the advantages of rapid effect [11], strengthening the heart, improving heart function, protecting vascular endothelial cells, regulating immune function, anti-inflammation and improving ability of hypoxia tolerance [12].

### Objective

The objective of this trial is to observe the influence of heart function and TCM syndrome and to assess the short-term effectiveness and safety in patients with AECHF due to CHD (*yang-qi* deficiency syndrome) treated with SFI loading.

## Methods

### Study design

This study is a prospective, randomized, multicenter, blind imitation, placebo-controlled trial. In order to avoid regional differences, participating centers include 12 hospitals located in the north and south of China. All cases included are hospitalized patients. Totally 160 subjects are randomly divided into treatment and control groups. The specific scheme is shown in Figure 1.

**Figure 1 Fig1:**
[figure not shown]
**Schedule of evaluations.** The overall plan of the trial and each step that needs to be performed is listed. CHF, chronic heart failure; SFI, Shenfu injection; GLI, glucose injection; NYHA, New York Heart Association; TCM, Traditional Chinese Medicine; LVEF, left ventricular ejection fraction; BNP, brain natriuretic peptide; 6MWD, 6-minute walking distance.

### Sample size

This is a clinical pilot trial; therefore, the total sample size of this study is determined to be 160 (during the trial, the expulsion rate is controlled within 20%) on expert advice. The treatment group and the control group have the same number of cases (that is, there are 80 cases in each group).

### Diagnostic criteria

#### Diagnostic criteria for coronary heart disease

The diagnostic criteria for CHD were: 1) history of myocardial infarction, with or without revascularization (percutaneous coronary intervention or coronary artery bypass grafting) treatment; and/or 2) coronary angiography or computed tomography coronary angiography confirmation of stenosis above 50% of at least one major branch of the coronary artery luminal diameter, with or without revascularization. A patient with one of these criteria is to be diagnosed with CHD.

#### Diagnostic criteria for acute exacerbation of chronic heart failure

According to *The diagnosis and treatment guideline for CHF of China in 2007* [13], *The diagnosis and treatment guideline for AHF of China in 2010* [2], *Executive Summary: HFSA 2010 Comprehensive Heart Failure Practice Guideline* [14], the diagnostic criteria for AECHF were: 1) having a medical history, symptoms or signs of heart disease, and the main symptoms and signs of dyspnea, fatigue, fluid retention (edema), jugular venous engorgement, and so forth; and 2) left ventricular ejection fraction (LVEF) ≤40% by the Simpson method.

#### Diagnostic criteria for cardiac function classification

Referring to the New York Heart Association updated version in 2005 [15], the criteria for heart functional class III were that the patients suffer from heart disease, and physical activity is significantly restricted (fatigue, palpitation, dyspnea or angina pectoris when the activity amount is less than normal), and for heart functional class IV that the patients suffer from heart disease, and physical activity is completely lost (symptoms of heart failure or angina pectoris are present even at rest, and any slight physical activity can make symptoms worse, for example dyspnea and fatigue).

#### The standardization of Traditional Chinese Medicine differentiation

According to *The Guidelines for Clinical Research of new TCM drugs (2002)* [16,17], the primary signs and symptoms are palpitation, shortness of breath (dyspnea), and fatigue. The secondary signs and symptoms are spontaneous perspiration, disinclination to talk, wheezing, cough, chest stuffiness (pain), loss of appetite, abdominal distension, aversion to cold, cold limbs, and edema. In addition, the tongue and pulse presentation is of a pale and dark tongue, which is fat or with indentation, and the pulse is sunken, slow or quick, or knotted and intermittent.

A patient must meet all the primary symptoms and at least two of the secondary symptoms listed above, consulted with the tongue and pulse presentation, to be diagnosed with *yang-qi* deficiency syndrome.

### Inclusion criteria

Patients aged 40 to 79 years;Diagnosis of CHD, AECHF;New York Heart Association Class II to IV;TCM diagnosis of *yang- qi* deficiency syndrome;Provision of written informed consent by participants or surrogates.

### Exclusion criteria

Patients with acute coronary syndrome (cardiac troponin T/ cardiac troponinI, creatine kinase-MB isoenzyme as screening index, acute myocardial infarction within 6 months, revascularization within the past 6 months or planned for revascularization within 1 week after inclusion, cardiogenic shock, lethal arrhythmia, cardiomyopathy, rheumatic valvular heart disease, myocarditis, constrictive pericarditis, pulmonary embolism, and so forth.Severe hepatic, renal insufficiency (alanine transaminase ≥3 times the normal upper limit, creatinine ≥3 mg/dL;Combined with the endocrine system, hematopoietic system and other severe primary diseases;Preparing for pregnancy within 3 months, pregnant, or breast-feeding women;Patients with psychosis;Patients with an allergic constitution, known sensitivity to the study drugs or their ingredients;Participation in other clinical trials within 3 months;Researchers estimate that the survival period of patient is not more than 3 months;Researchers estimate that the patient cannot complete or comply with the requirements of this study.

### Randomization

This study will use the central randomization system of the Tianjin Institute of Clinical Evaluation to achieve the distribution of patients and drugs.

The central randomization system will adopt age (40 to 49, 50 to 59, 60 to 69, and 70 to 79 years) and cardiac function classification as the central random control factors to dynamically and randomly allocate the participants, keeping a balance between the two groups to avoid selection bias; it will also monitor the real-time drug distribution and inventory information of each center in order to timely supply drugs and effectively avoid drug excess, saving the resources of manpower and materials.

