### Interventions

According to *The diagnosis and treatment guideline for AHF of China in 2010* [2] and *The diagnosis and treatment guideline for CHF of China in 2007* [13], doctors will choose medications based on conventional Western medicine treatment, and are prohibited from using other TCM in addition to the test drug. Combined with the cardiac function of patients, the basal therapy for CHF and AECHF are as follows: diuretics (furosemide injection for the first 7 ± 1 days and oral tablet during the follow-up period), angiotensin-converting enzyme inhibitors or angiotensin receptor blockers, β-blockers, aldosterone antagonists, digitalis, anti-platelet drugs, statin drugs, and so forth.

In order to reduce the bias of the test results, the control group is treated with 150 ml 5% GLI. The injection volume for the control group is therefore the same as the treatment group. All patients need to have a fasting blood glucose test and diabetic patients have to adjust the dose of insulin before participating in the trial.

The test drug is used as follows. For the treatment group: 50 ml SFI dissolved in 100 ml 5% GLI delivered via intravenous drip within 150 minutes, once a day; for the control group: 150 ml 5% GLI via intravenous drip within 150 minutes, once a day; both over 7 ± 1 days as a course.

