### Outcome measurements

#### Primary outcomes

The primary outcomes of the study include the effective rate on the improvement of heart functional class and TCM syndrome. TCM syndrome is evaluated by grading the quantitative score according to the primary symptoms and secondary symptoms. Two indices, which are measured before and after treatment, are simple measurements used to judge the degree of CHF. The severity of heart failure symptoms has a poor correlation with ventricular function, but is clearly associated with survival rate [3].

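### Centre is not an allocation factor, so balance of arms within the 12 hospitals and between north and south is left to chance: no bias, but a small, cheaply recovered loss of precision

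*Protocol article*

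**What the plan says.** The Randomization section describes a central system that allocates dynamically. It names age in four bands and cardiac class as the balancing factors: "60 to 69, and 70 to 79 years) and cardiac function classification as the central random control factors". The same sentence mentions centres again, but only because the system tracks drug distribution and stock at each of them. The system therefore holds the site identifier but is not said to balance on it.

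Other sections bear on whether site matters:

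- Study design gives the reason for the spread of sites: "In order to avoid regional differences, participating centers include 12 hospitals located in the north and south of China".
- Sample size states "the total sample size of this study is determined to be 160" and "there are 80 cases in each group". It gives no power calculation, because "This is a clinical pilot trial".
- Primary outcomes are effective rates on heart functional class and on TCM syndrome. Both are graded by clinicians; for the second, "TCM syndrome is evaluated by grading the quantitative score according to the primary symptoms and secondary symptoms".
- Interventions leaves background treatment to the treating physician within national guidelines: "doctors will choose medications based on conventional Western medicine treatment".
- Statistical analysis names t tests and chi-squared tests, with no centre term, and leaves further detail to a separate analysis plan that is not shown.
- Trial status reports that the study is at database testing and ready for data entry and statistics.

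**The concern.** Choosing hospitals in the north and the south brings regional variation into the sample. Only allocation or analysis by region or centre takes that variation out of the treatment comparison. The stated allocation rule does neither, and a later analysis plan cannot add a factor to an allocation already made.

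Site is a plausible source of variation here. Both primary outcomes depend on clinical grading, and background drugs are chosen locally. Secondary outcomes describes a unified BNP instrument and a standard procedure for echocardiography; the article describes no comparable step for the two primary outcomes. With few patients per hospital, uneven splits between arms are likely at some sites. Differences in grading habit or background care then add noise to both primary comparisons.

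**Working it through.** **Inputs from the protocol article.** 160 patients, 80 per arm (Sample size); 12 hospitals (Study design); age in 4 bands and cardiac class as factors (Randomization); NYHA Class II to IV, so 3 levels (Inclusion criteria). Actual site sizes and the number of hospitals per region are not given.

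**Assumptions, not in the documents.** Mean effective rate 60%; SD of the true effective rate between hospitals 10 to 20 points. For the simulations: biased coin 0.8, an assumed mix of age and class, and two regions of 6 hospitals each.

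**1. Plan's own figure.** 2 × 80 = 160 agrees. The total was set on expert advice, so there is no formula to reproduce.

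**2. Patients per hospital.** 160/12 = 13.3 on average; 160 × 0.8/12 = 10.7 if the full 20% loss allowed for occurs.

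**3. Split within a hospital of 13 when centre is ignored**, X ~ Binomial(13, 0.5):

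- 9:4 or worse: 2 × P(X ≥ 9) = 0.267; 12 × 0.267 = 3.2 hospitals expected.
- At least one hospital at 9:4 or worse: 1 − (1 − 0.267)^12 = 0.98.
- 10:3 or worse: 2 × P(X ≥ 10) = 0.092; at least one such hospital: 1 − (1 − 0.092)^12 = 0.69.

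**4. Does balancing on age and class help?** Hardly. Minimisation was simulated with near-equal sites (3,000 trials per row):

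| Factors | Mean arm difference per site | Sites differing by 5 or more | P(any such site) | Mean arm difference in share from one region | SD of chance shift, site SD 10 points |
|---|---|---|---|---|---|
| Age, class | 2.8 | 2.6 | 0.94 | 6.5 points | 1.5 points |
| Age, class, centre | 1.4 | 0.17 | 0.15 | 3.0 points | 0.8 points |

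With unequal sites, P(any site differing by 5 or more) goes from 0.90 to 0.10.

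**5. Bias and type I error.** The mean shift in the treatment difference was 0.00. Type I error of the unadjusted chi-squared test was 0.048, 0.047 and 0.050 for site SD 0, 10 and 20 points (20,000 trials each, random 80:80 allocation ignoring centre).

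**6. Cost in precision.**

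- Standard error of the rate difference: sqrt(2 × 0.6 × 0.4/80) = sqrt(0.0060) = 7.7 points; in squared points, 60.
- Centre's share of outcome variance, SD²/0.24: 0.01/0.24 = 4% and 0.04/0.24 = 17%.
- Variance of the chance shift, 4 × SD²/160: 4 × 100/160 = 2.5 and 4 × 400/160 = 10 squared points, so an SD of 1.6 and 3.2 points.
- These amounts are already inside the 60. Removing them gives sqrt(60 − 2.5) = 7.6 and sqrt(60 − 10) = 7.1 points.
- Reduction: 1 − sqrt(57.5/60) = 2% and 1 − sqrt(50/60) = 9%.

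**The case against.** The strongest reply is that little is at stake. Central random allocation makes arm unrelated to site in expectation, and the checks above show no bias and no excess type I error. A reader might infer that site differences are confounded with treatment, or left uncontrolled in a way that threatens validity. The documents do not support that. Nor should the chance shift of 1.6 to 3.2 points be added to the 7.7-point standard error, which already contains it.

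A reader might also infer that Study design and Randomization contradict each other. They do not. The sentence on regions explains the choice of hospitals and promises nothing about balance between arms. It is loosely worded, since choosing hospitals in both regions cannot remove differences between them.

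It can also be said that site variation is partly held down: cardiac class is balanced, treatment follows national guidelines, and evaluators are blinded. That is fair, and it argues for the lower end of the assumed range. Leaving centre out can be defended too. A 12-level factor makes allocation somewhat more predictable within a site, and the Blindness section says nurses are not blinded.

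Finally, a centre-adjusted analysis may be in the analysis plan that is not shown, so its absence cannot be asserted. All of this limits the size of the point. What stands is that the stated allocation rule leaves site and regional balance to chance.

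**Conclusion.** The point holds as a minor one. The allocation rule as stated does not balance arms within hospitals or between regions, and some hospitals very likely split unevenly: about 3 of 12 at 9:4 or worse if sites are of equal size. It would be too strong to say that every site will be uneven.

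The consequence is lost precision and chance regional imbalance, not invalid inference. The loss is about 2% to 9% of the standard error. That range rests on an assumed mean effective rate of 60% and an assumed between-hospital SD of 10 to 20 points, neither of which the article supplies; the upper end needs the larger SD. For a pilot sized on expert advice this does not threaten the trial, but the remedy is cheap enough to be worth taking.

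**What to change.** - **If any allocation remains:** add centre, or at least north/south region, as a factor in the dynamic allocation, and keep a random element so that the next assignment cannot be deduced at a site. The system already holds the site identifier, so this is one setting. The cost is slightly looser balance on age and class, and slightly more predictable allocation at sites where nurses know the treatment.
- **If allocation is complete, as Trial status suggests:** make the two primary comparisons stratified, for example Cochran-Mantel-Haenszel by region or pooled centre, in place of the plain chi-squared test, unless the analysis plan already does so. Fix this before unblinding. The cost is one stratification term. Pooling small hospitals is advisable, because a stratum with only one arm contributes nothing to a stratified test.
- **Wording:** change the Study design sentence to say that hospitals were chosen to sample both regions, not that regional differences are thereby avoided.

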### Blindness

Because SFI is a colored transparent liquid, nurses use the disposable light-proof infusion cover to effectively block the test drug and 5% glucose injection (GLI) in order to reduce bias. This study will blind doctors, evaluators, patients and statistical experts, but not the nurses.

### Interventions

According to *The diagnosis and treatment guideline for AHF of China in 2010* [2] and *The diagnosis and treatment guideline for CHF of China in 2007* [13], doctors will choose medications based on conventional Western medicine treatment, and are prohibited from using other TCM in addition to the test drug. Combined with the cardiac function of patients, the basal therapy for CHF and AECHF are as follows: diuretics (furosemide injection for the first 7 ± 1 days and oral tablet during the follow-up period), angiotensin-converting enzyme inhibitors or angiotensin receptor blockers, β-blockers, aldosterone antagonists, digitalis, anti-platelet drugs, statin drugs, and so forth.

In order to reduce the bias of the test results, the control group is treated with 150 ml 5% GLI. The injection volume for the control group is therefore the same as the treatment group. All patients need to have a fasting blood glucose test and diabetic patients have to adjust the dose of insulin before participating in the trial.

The test drug is used as follows. For the treatment group: 50 ml SFI dissolved in 100 ml 5% GLI delivered via intravenous drip within 150 minutes, once a day; for the control group: 150 ml 5% GLI via intravenous drip within 150 minutes, once a day; both over 7 ± 1 days as a course.

